### Study rationale

To date, no randomized controlled trial (RCT) has focused on the early administration of BBs in TBI patients based on the HsTnT status. BBs administration is still not the standard of care for TBI patients. However, prior observational studies have suggested that early low-dose propranolol can be safely administered and might improve outcomes after TBI [25, 27, 28] or severe trauma [29]. According to a recent meta-analysis [30], there is a single RCT that assessed the potential adverse events associated with BB therapy in TBI. There was no significant difference between the study groups in terms of the incidence of hypotension, bradycardia, heart failure, and bronchospasm.

The question of whether early administration of BBs has beneficial effect on the 10- and 30-day mortality in patients with mild-to-severe TBI based on the admission HsTnT status will be investigated in this study. Of note, there are various questions that need exploration such as (a) whether the severity of head injury alone or in combination with biomarkers will be a guide for the early use of BBs in TBI, (b) whether these biomarkers reflect the sympathetic surge only or the silent myocardial injury as well, and (c) whether these biomarkers have prognostic value only or they also possess diagnostic and therapeutic implications in TBI. To address this gap in the literature, we are undertaking a large double-blind RCT comparing protocolized, early administration of propranolol (within the first 24 h of hospital admission and after the HsTnT result) in the management of TBI patients. This study will be powered sufficiently to detect clinically relevant differences in all-cause mortality and neurological outcomes.

## Methods and study design

The Beta Blocker Use in Traumatic Brain Injury Based on the High-Sensitive Troponin T Status (BBTBBT) is a prospective double-blind RCT of BB use in TBI patients based on the HsTnT status. The primary hypothesis is that early propranolol administration is effective in reducing the10- and 30-day mortality.

### Participants and study setting

The trial setting is the Hamad level I Trauma Centre in the state of Qatar, and the study subjects will be screened and enrolled from the trauma room in the emergency department (ED). Inclusion criteria are adult patients (≥ 18 to ≤ 65 years old) who sustained mild-to-severe blunt TBI (head AIS 1-5 and/or GCS 4-15), screened and enrolled within the first 24 h post-trauma.

Exclusion criteria are non-survivable injuries (head AIS = 6 and GCS = 3), uncontrolled bleeding on arrival to ED, SBP ≤ 100 mmHg (or MAP < 70 mmHg) not responding to initial resuscitation or required to be maintained on vasopressors for persistent hypotension (up to 24 h), patients with bradycardia [HR < 60] (re-assess every 2 h), pregnant women, prisoners, known to have severe bronchial asthma, and who requires emergency surgery < 6 h and no longer under trauma team care.

We expect to recruit a total of 771 TBI patients over 2 years. On hospital arrival, all TBI patients will have an initial head CT scan and managed according to the Advanced Trauma Life Support (ATLS) guidelines. We have a neurocritical care team with the state-of-art monitoring, imaging, and management of TBI. For this study, all mild-to-severe TBI patients who required hospital admission will be screened and enrolled by the attending physician and assigned nurse, if the subject meets the eligibility criteria. All enrolled patients will be tested for HsTnT (on admission and to be repeated after 6 h if the first reading is normal) and those who had positive HsTnT will receive BB, if no contraindication (group 1). Subjects with negative HsTnT (2 consecutive tests) will be randomized to either group 2, HsTnT –ve and BB use, or group 3, HsTnT –ve and no BB (placebo) (SPIRIT, Fig. 1).

**Fig. 1 Fig1:**
[figure not shown]
BBTBBT protocol

Patients will be stratified based on the admission GCS prior to randomization. Serial electrocardiography (ECG) will be performed for all patients. Patients with abnormal ECG and/or positive troponin will also undergo transthoracic echocardiography, if indicated. Participant timeline is given in Table 1

**Table 1 Tab1:** BBTBBT timeline

Procedure/intervention/task	Day 1	Day 2	Day 3	Day 4	Day 5	Day 6	*Day 10	*Day 30	3-month
Selection criteria^1^	X								
Informed consent	X								
CT scan head^2^	X								
HsTnT^3^	X								
Vital signs^4^	X	X	X	X	X	X			
Randomization	X								
Treatment protocol^5^	X	X	X	X	X	X			
Electrocardiography (ECG)	X	X							
Echocardiography^6^	X								
Laboratory tests (S100B, enolase, cytokines (IL-1b,6,8,18))	X	X	X						
Serum epinephrine	X	X							
Routine blood tests^7^	X								
Glasgow Outcome Score (GOS)									X
Last day follow-up									X

1 = on admission, 2 = on-admission if hemodynamically stable and head injury suspected, 3= within 4 h and to repeat after 6 h, 4= continuous monitoring and to be documented before starting treatment, 5 = beta blocker vs. placebo within the 1st 24 h of admission, 6 = if troponin positive and ECG changes,7 = blood hemoglobin, platelet count, international normalized ratio, prothrombin time, activated partial thromboplastin time, blood glucose level, C-reactive protein, serum creatinine, urea, lactate, base deficit, sodium, and potassium, * = outcome (alive vs. dead)

### Outcome measures

The primary outcome is to determine whether early administration of propranolol based on the HsTnT status influences the 10- and 30-day mortality in TBI patients.Secondary *endpoints* include the effect of propranolol administration on the duration of hospital stay and functional status, measured using Functional Independence Measure (FIM) score at the latest time and Glasgow Outcome Score (GOS) at 3 months.We will also perform secondary exploratory analyses: (i) to correlate the HsTnT value with the serum S100 calcium binding protein B and enolase (markers of brain injury) value and the injury severity, (ii) to correlate the HsTnT value with the inflammatory markers and *e*pinephrine, and (iii) to examine the association between the HsTnT result and type of TBI lesion based on the CT scan.

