## Abstract

**Background:**

Beta-adrenergic receptor blockers (BB) play an important role in the protection of organs that are susceptible for secondary injury due to stress-induced adrenergic surge. However, the use of BB in traumatic brain injury (TBI) patients is not yet the standard of care which necessitates clear scientific evidence to be used. The BBTBBT study aims to determine whether early administration of propranolol based on the high-sensitive troponin T(HsTnT) status will improve the outcome of TBI patients. We hypothesized that early propranolol use is effective in reducing 10- and 30-day mortality in TBI patients. Secondary outcomes will include correlation between serum biomarkers (troponin, epinephrine, cytokines, enolase, S100 calcium binding protein B) and the severity of injury and the impact of BB use on the duration of hospital stay and functional status at a 3-month period.

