### Statistical analysis plan

The proposed sample size is based on an estimated rate of 12% reduction in mortality with the use of BBs in TBI patients reported by Salim et al. [13], having 80% power and 5% alpha error; the estimated sample size would be 257 subjects (including 5% dropout) in each study group (total 771 patients).

All analysis will be blinded to treatment assignment and will be performed by an independent biostatistician at Hamad Medical Corporation. We will also perform multivariate logistic regression analysis after adjusting for relevant covariates in addition to the differential intervention with an adjusted risk ratio and 95% confidence interval for the probability of death. Analysis will be based on intension-to-treat. Additional exploratory analyses will be performed for continuous variables such as marker of brain injury, injury severity scoring and head Abbreviated Injury Scale, cytokine level by comparing their distributions between intervention arms, and then by multiple linear regression models including other potential covariates of interest. We will explore the effectiveness of the intervention in subgroups using stratified analysis as well as multivariable models. The response to BBs use based on the type of brain lesion will be analyzed. Data analysis will be carried out using the Statistical Package for Social Sciences version 26 (SPSS Inc. USA).

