## Discussion

From the therapeutic point of view, BBs use was reported to have better survival in blunt TBI patients [4, 13, 14, 25, 26, 34–40]; however, double-blind RCTs remain lacking. Despite the optimistic results from prior data, a protocolized early BBs use is not currently a routine practice in patients sustaining TBI. Moreover, the release of cardiac troponin after head injury needs more scientific elaboration and physician awareness. A recent meta-analysis involving 12,721 patients showed that administration of BBs after TBI was associated with a significant reduction in adjusted in-hospital mortality (OR, 0.39) [35]. Retrospectively, Salim et al. [13] reported that patients with severe TBI who did not receive BBs had a mortality rate of 36% vs. 24% in those who received BBs (*p* = 0.036). Furthermore, if troponin-I was elevated on admission, the hospital mortality increased to 48.5% in patients without BBs therapy vs. 22.4% in those who received BBs (*p* = 0.026). In brief, the greatest survival benefit was observed retrospectively in the BBs group based on the conventional troponin positivity on admission.

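### Day-10 and day-30 mortality are both primary, but the sample size covers one test at one 5% level with no success rule; separately, logistic regression is paired with a risk ratio.

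*Protocol article*

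**What the plan says.** All places are in the protocol article.

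- **Primary outcome.** Outcome measures defines it as whether early propranolol "influences the 10- and 30-day mortality in TBI patients". The abstract ("We hypothesized that early propranolol use is effective in reducing 10- and 30-day mortality in TBI patients") and Methods and study design ("early propranolol administration is effective in reducing the10- and 30-day mortality") use the same pair. Table 1 reads vital status at both days. Neither day is put first, and the word joining them is not defined as both-required or either-sufficient.
- **Sample size.** The Statistical analysis plan section uses an "estimated rate of 12% reduction in mortality with the use of BBs in TBI patients", "having 80% power and 5% alpha error", and arrives at 257 per group including 5% dropout (771 in total). No day is attached to the reduction. The Discussion gives the rates behind it: patients with severe TBI who did not receive beta blockers "had a mortality rate of 36% vs. 24% in those who received BBs".
- **Effect measure.** The same section adds a multivariable logistic regression, reported "with an adjusted risk ratio and 95% confidence interval for the probability of death". It gives no step from the logistic coefficient to a risk ratio.

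**The concern.** The stated alpha, power and sample size describe one test, while the stated primary outcome contains two. The reader therefore cannot tell which result would count as success. If either day may win, the false-positive rate is above 5%, and the favourable day could be chosen after the data are seen. If both must win, the false-positive rate is protected, but the 80% power was not calculated for that requirement.

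The second matter is separate. A logistic model's exponentiated coefficient is an odds ratio. When death is common, an odds ratio lies further from 1 than the risk ratio, so reading one as the other overstates the relative benefit.

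**Working it through.** **Inputs from the article:** 36% vs 24% (Discussion); two-sided 5% (sidedness inferred, see step 1), 80% power, 5% dropout, 257 per group (Statistical analysis plan); 1:1 allocation among troponin-negative patients (Randomization). **Assumptions:** the share f of 30-day deaths that occur by day 10, and the 30-day mortality under the null, since the article gives neither.

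**1. The plan's own figure.** For two proportions, n = [1.96·√(2·0.30·0.70) + 0.842·√(0.36·0.64 + 0.24·0.76)]² / 0.12² = 227.7. With continuity correction, n = (227.7/4)·[1 + √(1 + 4/(227.7·0.12))]² = 244.1. Dividing 244 by 0.95 gives 256.8, which is the stated 257. (Rounding up to 245 first gives 258.) One-sided versions give 190 or 207, and two-sided without correction gives 240. The 257 is therefore one comparison at a full two-sided 5%, with no allowance for a second primary test.

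**2. Either day suffices.** Day-10 deaths are a subset of day-30 deaths, so the two test statistics are correlated: ρ = √[p10(1−p30) / (p30(1−p10))], with p10 = f·p30. Type I error is P(|Z1|>1.96 or |Z2|>1.96) under a bivariate normal. The lowest p30 used, 8.8%, is derived from the Introduction's figures for the centre (26% mortality overall, 65% troponin-positive, four-fold mortality in positives): 0.26/(0.35 + 0.65·4) = 0.088.

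| p30 | f = 0.5 | f = 0.7 | f = 0.9 |
|---|---|---|---|
| 8.8% | 8.4% | 7.6% | 6.5% |
| 26% | 8.6% | 7.8% | 6.7% |
| 36% | 8.7% | 8.0% | 6.8% |

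The range is about 6.5-8.7%. Treating the tests as independent would give 9.75%, which is too high for nested outcomes.

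**3. Both days required.** Simulation with 244 per arm, 36% vs 24% at day 30, 200,000 runs:

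| f | Day 10 alone, RR 0.67 at both days | Both, RR 0.67 at both days | Both, full 12 points already present at day 10 (f applies to control deaths) |
|---|---|---|---|
| 0.6 | 54% | 53% | 82% |
| 0.7 | 63% | 61% | 81% |
| 0.8 | 70% | 68-69% | 80% |
| 0.9 | 77% | 75% | 80% |

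Day 30 alone has 83%. Under the null with 30% mortality in both arms, both tests are significant in 1.8-3.3% of runs, so type I error stays below 5%.

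**4. Splitting alpha instead.** At 0.025 per day, the same corrected formula gives 293 per group, or 309 with dropout. With 244 evaluable per group, power at 0.025 is about 74%, against 83% at 0.05 (both uncorrected).

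**5. Odds ratio against risk ratio.** At the planning rates, RR = 0.24/0.36 = 0.667 and OR = (0.24/0.76)/(0.36/0.64) = 0.561. An odds ratio labelled as a risk ratio would show a 33% reduction as 44%. Holding RR at 0.667:

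| Control mortality | OR | Apparent reduction |
|---|---|---|
| 36% | 0.561 | 44% |
| 26% | 0.597 | 40% |
| 10% | 0.643 | 36% |
| 8.8% | 0.646 | 35% |

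**The case against.** The strongest reply is that the hypothesis joins the two days with the word and. On its plain reading both are claimed, so type I error stays at or below 5%. No either-day rule appears anywhere, and a success rule is often left to an analysis plan that is not shown here. It stands that an inflated error rate cannot be asserted as fact: a reader might infer it, but it follows only if either day may win. What does not fall away is the mismatch among elements that the article itself fixes. It states the primary outcome, alpha, power and sample size, and together they describe one test for two endpoints.

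A reader might also infer that requiring both days can never reach 80% power. The documents do not support this. The 12 points are tied to neither day, treatment lasts six days, and if the whole effect is present by day 10, joint power is 80-82%. The shortfall depends on the constant-risk-ratio assumption.

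On the effect measure, a logistic model can give a valid adjusted risk ratio by marginal standardisation, so the plan is achievable as written. The model is introduced as an additional analysis, so calling its result the trial's main effect estimate would be inference, although it is the only effect measure named for death. The 44% figure rests on rates from a retrospective study of severe TBI. The randomised patients are troponin-negative with mild-to-severe injury, and at lower mortality the gap nearly closes.

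**Conclusion.** The concern holds in a conditional form. Two unranked primary time points share one alpha and one sample-size calculation, with no success rule.

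- If either day may win, type I error is about 6.5-8.7% (30-day mortality 8.8-36%, 50-90% of those deaths by day 10).
- If both must win, alpha is protected. Power is about 53-75% under a constant risk ratio of 0.67 with 60-90% of deaths by day 10, and about 80-82% if the full 12 points are present by day 10.

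The model and the promised measure do not match without a conversion step that the article omits. If an odds ratio were labelled as a risk ratio, a 33% reduction would appear as 35-44%, depending on control mortality. The documents do not show that the reported effect will be wrong, only that the wording leaves room for it.

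**What to change.** 1. Name all-cause mortality at 30 days, group 2 versus group 3, as the single primary endpoint, tested once at two-sided 5%. This is the comparison that is randomised.
2. Tie the 12-point reduction to that endpoint.
3. Test 10-day mortality next, in fixed order, only if the 30-day result is significant.
4. Obtain the adjusted risk ratio by modified Poisson regression with robust variance, or by marginal standardisation of the logistic model. Otherwise, report the result as an odds ratio.

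A both-required rule or an alpha split would also settle the first matter. The former needs its joint power stated under explicit assumptions about early deaths, and an even split needs about 309 per group. Fixed order keeps 5% and 257 per group. The cost is wording in the protocol, analysis plan and registry entry, and day 10 loses co-primary status.

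### Duration of hospital stay is truncated by death, the primary outcome, so a mortality benefit can lengthen mean stay and be read as harm

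*Protocol article*

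**What the plan says.** In the protocol article, Outcome measures names "the effect of propranolol administration on the duration of hospital stay and functional status" as secondary endpoints. The abstract's Background lists "the impact of BB use on the duration of hospital stay and functional status at a 3-month period" among the secondary outcomes. The primary outcome, in the same Outcome measures section, is whether propranolol "influences the 10- and 30-day mortality in TBI patients".

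The Statistical analysis plan section bases the sample size on "an estimated rate of 12% reduction in mortality with the use of BBs in TBI patients". The rates behind that figure are in the Discussion, where a retrospective study reports that "patients with severe TBI who did not receive BBs had a mortality rate of 36% vs. 24% in those who received BBs". The same section specifies an intention-to-treat analysis. It gives logistic regression for death, and distribution comparisons with linear regression for exploratory continuous variables such as biomarkers and severity scores. It names no method for hospital stay. No section says how a patient who dies in hospital enters the stay comparison.

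**The concern.** Hospital stay ends in discharge or in death, and a bare duration does not tell the two apart. A patient who dies on day 5 and one who goes home on day 5 have the same value, although one outcome is the worst possible and the other is good. The trial is designed to change the number of deaths, so it is designed to change the mix of reasons for which stays end.

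If propranolol prevents early deaths, short stays ending in death are replaced by longer stays ending in discharge. Mean stay rises in the arm that did better on the primary outcome, and a reader may take this as a cost of treatment. If propranolol causes early deaths, mean stay falls and looks like a gain. Dropping the deaths does not help: survivors are a group selected after randomisation, and patients saved by treatment appear among the survivors of one arm only.

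At stake is the direction of one secondary conclusion. It has some practical weight because the article also hopes to show reduced health care cost.

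**Working it through.** **1. The plan's own figure.** Inputs: 36% versus 24% (Discussion), and "having 80% power and 5% alpha error" (Statistical analysis plan). The article does not state sidedness, so a two-sided test is assumed. A comparison of two proportions with continuity correction needs 245 per group. Allowing for 5% dropout gives 245 / 0.95 = 257.9, or 245 × 1.05 = 257.25. The article states "257 subjects (including 5% dropout) in each study group (total 771 patients". The figure reproduces to within rounding, so 36% versus 24% is the planning scenario. Without the continuity correction the result is 228, or 240 after dropout, which does not match.

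**2. Formula for the artefact.** Let m be mortality, S the mean stay of survivors and D the mean time to death. Mean stay = (1 − m) × S + m × D. If treatment changes nothing except m, the difference (propranolol minus placebo) is (m_placebo − m_propranolol) × (S − D). The article gives neither S nor D; the values below are assumptions.

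**3. At the planning rates, 36% versus 24%.**
- S = 20, D = 5: placebo 0.64 × 20 + 0.36 × 5 = 14.6; propranolol 0.76 × 20 + 0.24 × 5 = 16.4; difference +1.8 days.
- S = 10, D = 3: 0.12 × 7 = +0.84 days.
- S = D = 15: 0.12 × 0 = 0 days.
- S = 15, D = 30: 0.12 × (−15) = −1.8 days. The sign reverses when deaths come later than discharge.

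**4. At rates closer to the randomised patients.** Only troponin-negative patients are randomised (Randomization). The Introduction reports, from a study at the same centre, 26% mortality, a rate 4-fold higher in troponin-positive patients, and 65% positive in moderate to severe TBI. Let q be mortality in negatives. Then 0.35q + 0.65 × 4q = 0.26, so q = 0.26 / 2.95 = 8.8%. Assuming the same relative reduction as in planning (24/36), the treated rate is 5.9% and the difference is 2.94 percentage points.
- S = 20, D = 5: 0.0294 × 15 = +0.44 days.
- S = 10, D = 3: 0.0294 × 7 = +0.21 days.

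**5. How often a test would point the wrong way.** Simulation: 257 per arm, lognormal stays (SD 0.8 on the log scale), mean 15 days for survivors and 5 for deaths, two-sided Mann-Whitney test at 5%, 2,000 runs. The chance rate in one direction is 2.5%.

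| Mortality | Further assumption | Mean difference (days) | Significantly longer stay in the life-saving arm |
|---|---|---|---|
| 36% vs 24% | saved patients stay as long as other survivors | +1.15 | 33% |
| 36% vs 24% | saved patients stay 1.5 times as long | +2.07 | 55% |
| 36% vs 24% | 1.5 times as long, and a true 20% shorter stay in those who survive either way | +0.18 | 6% |
| 36% vs 24% | deaths have the same mean stay as survivors (15 days) | 0.0 | 2.4% |
| 8.8% vs 5.9% | saved patients stay as long as other survivors | +0.24 | 6% |
| 8.8% vs 5.9% | saved patients stay 1.5 times as long | +0.51 | 8% |

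In the third row a real benefit for survivors is almost completely hidden.

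**6. The alternative measure.** Days alive and out of hospital to day 30, with S = 20 and deaths scored as zero: 0.64 × 10 = 6.4 on placebo and 0.76 × 10 = 7.6 on propranolol. The life-saving arm is ahead. At 8.8% versus 5.9% the values are 0.912 × 10 = 9.1 and 0.941 × 10 = 9.4.

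**The case against.** The strongest reply is that the article only names the endpoint. It does not say that raw stay including deaths will be compared, and intention to treat keeps patients in their arm without saying how a death is scored. A rule for deaths is often left to a statistical analysis plan, and that document is not shown. This part stands: the absence of a rule is not itself the defect, and a reader should not infer that the plan scores an early death as a favourable short stay. The choice of endpoint, however, is made in the article. A duration of stay must either count deaths at face value or set them aside, and neither gives a sound randomised comparison. A rule that ranks death worst, or treats it as a competing event, turns the endpoint into a different one, which is the change asked for.

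The second reply is that 36% versus 24% comes from a retrospective study of severe TBI, whereas this trial randomises troponin-negative patients with mild-to-severe injury. This also stands, and it cuts the artefact to about a quarter.

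The third reply is against the tempting stronger claim that the propranolol arm will look worse whenever the drug saves lives. The documents do not support that. Direction and size depend on when deaths occur, how long saved patients stay, and whether propranolol changes stay in other survivors. The article gives none of these.

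Finally, mortality is the primary outcome, so stay would be read beside the deaths. That lowers the risk of misreading but does not make the stay comparison interpretable.

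**Conclusion.** The concern holds in a limited form. As an efficacy endpoint, duration of hospital stay is poorly chosen here because the primary outcome truncates it: a mortality benefit can lengthen it and excess early deaths can shorten it.

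Under the assumed stays, the artefact is 0.8 to 1.8 days at the planning rates and about 0.2 to 0.4 days at the mortality more likely in the randomised patients. At the planning rates it can often produce a significant result in the wrong direction; at the lower rates it does so only somewhat more often than chance.

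The 8.8% is approximate. It applies a positive share from moderate to severe TBI to a trial that also enrols mild cases, who would probably lower it, and the treated rate of 5.9% assumes the planning study's relative reduction. The point is worth correcting, but it touches one secondary endpoint only. The primary analysis and the sample size are unaffected.

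**What to change.** Replace duration of hospital stay as the secondary efficacy endpoint with one of these:

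- days alive and out of hospital to a fixed day, with death by that day scored as zero; or
- time to live discharge, with death as a competing event.

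Report raw stay descriptively, separately for patients discharged alive and for those who died, without a between-arm test.

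No new assessment should be needed. Measuring stay already requires the discharge or death date, and Table 1 schedules vital status at day 30. The cost is a change of endpoint wording and a small change of analysis. The new measure is less familiar than length of stay, and days alive and out of hospital partly overlaps with mortality, so it is not independent support for the primary result. A cut at day 30 ignores later stay. Follow-up runs to 3 months, so a later fixed day is possible if discharge dates and vital status are recorded to that point.
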